### Study setting

The study will be developed in an urban ICH “Parc Sanitari Pere Virgili,” Barcelona, Spain. The facility includes 360 inpatient beds, divided into geriatric rehabilitation, subacute care, palliative care, and long-term care, and approximately 40 hospital-at-home beds.

Patients will be included from the five geriatric rehabilitation wards. Most of the admitted patients usually come from a hip fracture or a stroke, or they are admitted following a stay in an acute care ward. The medical staff consists of geriatricians and general practitioners, and multidisciplinary team includes nurses, pharmacists, physiotherapists, occupational therapists, psychologists and social workers, among others. The average length of stay per patient is around 30 days.

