### Outcomes

The primary outcome of the study is the mean number of medications per patient.

Secondary outcomes are (see also “Participant timeline and data collection”): prevalence of quantitative polypharmacy and hyperpolypharmacy, qualitative polypharmacy, PIMs, anticholinergic burden, number of underprescribed medications that have been started, ADEs and adverse drug withdrawal events (ADWEs), unplanned care utilization, and mortality. Patient-reported outcome measures (PROMs) will also be secondary outcomes for this study. They include adherence, treatment burden, perceived health status and quality of life, health literacy, and attitudes on deprescription (see Table 1). Finally, another secondary outcome will be the identification of barriers and facilitators of the implementation of the purposed methodology, both at the level of the individual person/healthcare professionals (possible cultural aspects, preferences, etc.) as well as from the system point of view (aspects related to intermediate care).

**Table 1 tab1:** Detailed collected variables.

Demographic variables	Multidimensional assessment	Medication assessment	PROMs

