### Participant timeline and data collection

Enrolled patients will be evaluated upon admission for the variables detailed in Table 1 (baseline assessment) and undergo medication review (see “Interventions”). Since the planned intervention will be performed upon hospital admission, we expect nearly total retention. In detail, a trained clinical pharmacist and a geriatrician will perform an evaluation on demographic data, a brief multidimensional geriatric assessment, including the evaluation of the frailty, and data on quantitative/qualitative polypharmacy.

For the intervention phase, PROMs will be assessed upon admission through an interview conducted by a trained clinical pharmacist (see Table 1). Figure 3 summarizes the timeline for the intervention phase.

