In detail, we will evaluate alert diagnoses: unexpected clinical manifestations occurring during the admission and that might be related or unrelated to the use (or lack of use) of a certain medication. We will also evaluate previously defined altered laboratory tests, according to reference laboratory and literature review. Finally, we will evaluate alert drugs: medications known to be used to correct an alteration produced by a first medication (e.g., naloxone to reverse opioid overdose). All triggers will be further reviewed to discern if they are clearly independent from clinical manifestations related to the patients’ condition. Causality will be then assessed using the 10-point Naranjo Scale (33). The severity of the event will be classified using a modified Hartwig and Siegel scale (34), ranging from trivial (event does not require additional treatment and as no sequalae) to fatal. Avoidability of the event will be assessed using a modified Schumock and Thornton questionnaire (35). Each potential ADE/ADWE form will be evaluated by the blinded members of the ADE/ADWE Adjudication Committee, consisting of a geriatrician and a clinical pharmacist not directly involved in the retrospective review process. In the case of disagreement, additional review by another blinded geriatrician/clinical pharmacist pair of evaluators will be requested. Also, 90 days post-discharge (post-discharge assessment), both experimental and control phase participants will be re-evaluated for quantitative polypharmacy, PROMs, unplanned health care utilization (acute hospital admission, emergency claims), and mortality.

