### Data analysis

Baseline variables will be described using means and standard deviations for quantitative variables and absolute and relative frequencies for categorical variables, with their corresponding 95% confidence intervals. The Student’s t-test will be used to compare means of medications and other qualitative variables, and the chi-squared test will be used to compare polypharmacy, hyperpolypharmacy, ADEs, ADWEs, and other categorical variables. All analyses will be stratified according to frailty and to age groups, as appropriate.

We will perform a generalized lineal model with mixed effects for (individual) time and cluster. In the descriptive analysis we also will perform descriptions for each cluster. The ICC for within-cluster correlation will be analyzed and recalculated with the data result and included in a sensitivity analysis.

Multivariable analyses will be carried out to assess the association between decrease in the number of medications at discharge and possible determinants. PROMs will be assessed by comparison of scores before and after the intervention by using paired t-test for continuous variables and McNemar’s test for categorical variables. Cox proportional hazard models will be used to evaluate the association between intervention and survival or time to first unplanned health care utilization. Missing data will be handled according to multivariate imputations by chained equations. Interim analyses are not planned.

All the analysis of secondary outcomes will only be exploratory as far as the sample size is not powered to detect differences on these variables.

All analyses will be carried out according to the intention-to-treat principle, with statistical significance at *p* < 0.05. STATA and R-Studio software will be used in their most recent versions available for statistical analysis.

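### The only analysis assigned to PROMs is a within-patient before-after test, so change after an acute event cannot be separated from the effect of the intervention

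*Protocol article*

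**What the plan says.** - **Status.** The Outcomes section says: "Patient-reported outcome measures (PROMs) will also be secondary outcomes for this study". The abstract lists them among the outcomes on which the intervention's impact will be evaluated.
- **Collection at 90 days.** Participant timeline and data collection says that, 90 days after discharge, "both experimental and control phase participants will be re-evaluated for quantitative polypharmacy, PROMs, unplanned health care utilization" and mortality. Control-phase PROM data will therefore exist at follow-up.
- **Collection at admission.** The same section opens with "Enrolled patients will be evaluated upon admission for the variables detailed in Table 1 (baseline assessment", and Table 1 includes the PROMs. It then adds: "For the intervention phase, PROMs will be assessed upon admission through an interview conducted by a trained clinical pharmacist". No matching sentence covers the control phase.
- **Analysis.** Data analysis says: "PROMs will be assessed by comparison of scores before and after the intervention by using paired t-test for continuous variables", and names McNemar's test for categorical PROMs. It also says: "We will perform a generalized lineal model with mixed effects for (individual) time and cluster", without tying that model to an outcome or naming an intervention term. Secondary analyses are qualified: "All the analysis of secondary outcomes will only be exploratory as far as the sample size is not powered" for them.
- **Population.** Study setting says: "Most of the admitted patients usually come from a hip fracture or a stroke", or are admitted after a stay in an acute ward.

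**The concern.** A stepped-wedge trial estimates an effect by comparing patients treated under the intervention with patients treated under control, allowing for calendar time and ward. A paired test of admission against follow-up scores makes no such comparison. It asks whether scores changed, and they may change under usual care as well.

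Patients enter rehabilitation shortly after an acute event and are asked again 90 days after they leave. Quality of life and self-rated health could well shift over that interval whatever was done to the prescriptions. If scores improve naturally, the test credits the improvement to person-centred prescription. If they decline, it can hide a benefit or suggest a harm. At stake is whether any statement about the intervention and PROMs can rest on the randomised design.

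**Working it through.** **1. What the paired test can compare.** Patients are selected at admission, each square of the design holds 10 patients (Figure 1 legend), and the total is 300 subjects (Sample size and recruitment). Five wards × 6 periods (baseline plus five) × 10 = 300, which reproduces the stated sample size, so each patient belongs to one ward-period. No patient is observed in both phases, and no pairs exist across phases. The pairs can only be admission and 90 days post-discharge in one person.

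**2. Number of intervention-phase patients.** All wards start in control and one crosses at each of five steps. Intervention cells: 5 + 4 + 3 + 2 + 1 = 15. Patients: 15 × 10 = 150, leaving 150 in control.

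**3. Rejection rate with no intervention effect.** The article gives no PROM figures, so the drift d is an assumption, in SDs of the change score. Two-sided 5% is assumed, since the article gives 0.05 without sidedness. The test statistic is noncentral t with 149 degrees of freedom and noncentrality d × √150.

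| Drift d | d × √150 | Significant, independent patients | Significant, change-score ICC 0.05 (simulated) | Between-phase model (same simulation) |
|---|---|---|---|---|
| 0 | 0 | 5% | 25% | 5.1% |
| 0.1 | 1.22 | 23% | 37% | 5.1% |
| 0.2 | 2.45 | 68% | 62% | 4.9% |
| 0.3 | 3.67 | 96% | 84% | 5.4% |
| 0.5 | 6.12 | about 100% | 99% | 4.2% |

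The last two columns come from 4,000 simulated trials per row. The between-phase model has period effects, an intervention effect and a random ward effect, with the assumed ICC of 0.05 treated as known. In practice it must be estimated from five wards, so the 4% to 5% is a best case. At zero drift the 25% arises only because the paired test ignores wards.

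**4. The same on the scale of the score itself.** With before-after correlation r, the SD of the change is √(2(1 − r)) score SDs. At r = 0.5 this is 1, so the two scales agree: the standard error is 1/√150 = 0.0816, a drift of 0.25 SD gives z = 0.25/0.0816 = 3.06, and the test rejects in about 86% of trials. At r = 0.3 the figure is about 74%, at r = 0.7 about 98%.

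**5. Precision given up by the valid comparison.** The Hussey-Hughes variance for this layout, with I = 5 wards, s² = (1 − 0.05)/10 = 0.095 and t² = 0.05, is 5 × s² × (s² + 6t²) / (20s² + 70t²) = 5 × 0.095 × 0.395 / (1.9 + 3.5) = 0.0347. The standard error is 0.186 SD of the change score, against 0.0816 for the paired test: about 2.3 times as large. The paired test looks more precise because it estimates something else and ignores wards.

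**The case against.** Several points on the other side stand.

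- **PROMs are secondary and exploratory.** The primary outcome, number of medications, is untouched, which lowers the weight of the point. But the article gives lack of power as the reason for the label. Low power concerns imprecision, whereas the fault here is bias, and the 0.05 threshold is applied to all analyses.
- **A reader might infer that control patients are never used for PROMs.** The text does not go that far. The paired test is not expressly confined to intervention patients, and neither the mixed model nor the Student's t-test, listed for medication means and other variables, excludes PROMs. What can be said is that the only method assigned to PROMs is the paired one. Running it separately in each phase would still not test the difference between phases.
- **A reader might infer that a false benefit is almost certain.** That depends on the drift. At 0.1 SD the rate is 23%, ward clustering lowers the rate at the larger drifts, and deaths or non-response by 90 days would leave fewer than 150 pairs.
- **A reader might extend the recovery argument to every PROM, or add regression to the mean.** The documents give no reason to expect adherence, treatment burden, health literacy or attitudes to deprescribing to improve spontaneously, and eligibility does not select on any PROM score.
- **A reader might call the admission PROM wording a contradiction.** It is an ambiguity. The opening sentence covers all enrolled patients, and being re-evaluated at 90 days suggests an earlier assessment in both phases. The intervention-phase sentence may only describe the patient interview that forms part of the intervention.

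**Conclusion.** The point holds in limited form. The method written for PROMs estimates change over time within patients and cannot attribute that change to the intervention, although the control-phase data needed for a valid comparison are already to be collected. The problem is greatest for EuroQoL-5D and self-rated health. Under no intervention effect the paired test would be significant in about 23% to 96% of trials for a drift of 0.1 to 0.3 SD of the change score. Those figures rest on an assumed drift, 150 complete and independent pairs, and a two-sided 5% test. The conclusion itself does not depend on the size of the drift, because the stated test contains no comparison between phases. The consequence is confined to the PROM conclusions.

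**What to change.** In Data analysis, replace the paired t-test and McNemar's test as the inferential method for PROMs:

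- Compare 90-day PROM scores between intervention and control phases in a mixed model with fixed intervention and period effects and a random ward effect, using a logistic version for categorical PROMs. State the intervention term explicitly, since the model sentence now in the article has none.
- Use a small-sample correction, because there are only five wards.
- Adjust for the admission score if it is collected in both phases. In Participant timeline and data collection, state whether control patients give admission PROMs. If they do not, compare the 90-day scores without that adjustment.
- Keep the paired before-after change, by phase, as description only.

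The cost is a change of wording and slightly more analysis work, with no new follow-up data. Some interview time is added only if admission PROMs have to be introduced for control patients, and that should be settled before recruitment because missing baselines cannot be recovered. Intervals will be wider than those from the paired test, about 2.3 times under the assumptions in the working.

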## Discussion

The aim of the AMIDA-ICH trial is to evaluate the implementation and effectiveness of multidisciplinary PCP intervention for improving medication appropriateness in older adults to intermediate care hospitals. The idea of this project was conceived in the context of intermediate care, where patients with lower intensive care needs may benefit the most from a structured PCP. This is due to various reasons. First, the type of patients, often older, with a significant comorbidity burden, and a higher risk of adverse events because of their degree of frailty. As a result, they are also more likely to chronically take multiple medications, making them ideal candidates for PCP. Additionally, the reasons for their admission have often led to a worsening of the above-mentioned frailty status. However, PCP might also help improve frailty by aligning care with patients’ goals, as well as with medical, functional, and cognitive improvements. Furthermore, the involvement of a multidisciplinary team of specialists (including clinical pharmacists alongside the other “geriatric healthcare staff”) can, on the one hand, support frailty management, and, on the other, monitor potential complications that may arise during the process. This study is part of an established clinical and research framework in the centre where the research will take place, and this could contribute to the appropriateness and success of the project. The patients’ length of stay may also facilitate this process, ensuring the implementation of PCP.

A recent update of a Cochrane systematic review of 25 trials involving more than 15,000 patients, especially older ones, demonstrated that medication review likely reduces hospital admissions (38), and this is of particular importance, since it is known that the general population suffers from a significant deficit in therapeutic adherence and quality of care, posing a threat to public health (39). Focusing on intermediate care settings, it has been found that patients usually have a high prevalence of PIMs upon admission (40, 41), and it seems to be also associated with non-adherence to the pharmacological treatment (42). Nonetheless, it has also been demonstrated that intermediate care services may help reduce this inappropriateness (40, 41). Anyway, in order to derive a solution, a Spanish quasi-experimental study conducted on 93 patients, 81% of whom showing mild–moderate frailty, with an average age of 83 years, and a history of taking 5 or more medications for at least 3 months, showed that the PCP approach increased adherence, and reduced inappropriate prescriptions (21). The same group has provided additional evidence on the efficacy of PCP even in other settings, and the importance of tailoring treatments according to the patients’ goals (18, 19, 43). In spite of a solid methodology, all these studies are limited by relatively small sample sizes. Further evidence came from the D-PRESCRIBE cluster randomized trial, conducted in older community-dwelling people. It was found that a pharmacist-led intervention to patients and prescribers is more effective than the usual care in achieving deprescription (relative risk for discontinuation: 3.55) (44). Additionally, the INCREASE randomized-controlled trial, also involving older community-dwelling people, compared the usual recommendations on polypharmacy with an approach including a meeting with a pharmacist and a nurse or physician. It revealed that about 40% of “baseline” recommendations were revised following the meeting with specialists (45). Hence, these findings highlight the need for a strategy including different professionals, and the PCP itself is inherently complex and multidimensional. Additionally, since professionals alone might not suffice in the context of multidimensionality, the role of the patient should not be merely “passive.” This is why we decided to incorporate PROMs into the quantitative part of our complex intervention trial. To achieve our aims, we have designed a complex intervention study, including both a quantitative component, following the stepped-wedge trial design, and a qualitative part, with interviews and focus groups. There is not a universally accepted interpretation of complex interventions, but they generally include varying degrees of targets, flexibility, and interactions required (46). Therefore, the effectiveness of our intervention will surely largely depend on its implementation (47, 48), which is why we have chosen this design. Implementation is defined as the complex of strategies designed to support health interventions, with the aim of translating an intention into action (49–51), and we believe that, as mentioned, the AMIDA-ICH program fits within this scenario. Our aim is not only to evaluate the intervention’s efficacy in terms of “conventional” outcomes, such as a potential reduction of the number of medications per patient (our primary outcome), or even decreases in ADEs, but also to assess “implementation outcomes” (52). In particular, a significant role will be given to adherence, feasibility, and treatment burden, allowing us to evaluate the real-world applicability of our model, leveraging the perspectives of health professionals, patients, and caregivers.

We also acknowledge certain limitations and risks. First, the 90-day follow-up after discharge may vary among the patients, as some may stay at the ICH for longer or shorter periods, influencing the likelihood of following the appropriate therapeutic regimen. Also, we will not conduct specific interventions addressing the various geriatric domains (e.g., cognitive, affective, functional, nutritional), which would vary case by case and could likewise potentially confound the primary and secondary outcomes of the study, also considering the broad inclusion criteria. Moreover, as a monocentric study and the use of a reduced number of clusters, the reproducibility of our findings may be limited. The inclusion of additional centers could have strengthened the potential validity of the evidence deriving from the study. Additionally, given the multidisciplinary nature of the intervention, the applicability and reproducibility of the results in hospitals that are not specifically organized to provide comprehensive assessment and care of older people cannot be assumed and may be limited.

While our hospital maintains stable teams for each ward, we recognize that certain situations could lead to a risk of contamination. If the research team identifies a significant risk in this regard, recruitment may be withhold until the situation stabilizes.

Finally, regarding the sample size, statistical power was set to 75% for the primary outcome in order to guarantee viability of the project and we used previous data from a single center study. Thus, the results will have to be interpreted taking into consideration a possible overestimation of the effect.

Nonetheless, we also acknowledge several strengths. First, its mixed-model design, which is quite original in the literature. Additionally, the use of clusters may facilitate the implementation of the model. Furthermore, considering medications from both qualitative and quantitative perspectives, along with potential ADE/ADWEs, is crucial to enhancing the scientific value of the study, and providing more information on the model’s efficacy and safety.

Unlike previous studies (21, 28, 41, 44, 45), this trial combines a stepped-wedge cluster randomized design with an implementation science framework and an embedded qualitative evaluation. The intervention integrates multidisciplinary medication review, patient-reported outcome measures, and patients’ preferences within the intermediate care setting, providing evidence not only on effectiveness but also on implementation processes and contextual determinants.

To sum up, we believe that this study will offer a contribution to improving prescription appropriateness and reducing adverse events, particularly in the most vulnerable subjects, namely older, frail individuals with multiple comorbidities. By tailoring treatments to individual patient needs and preferences, we could enhance safety and efficacy of pharmacological interventions. Furthermore, as a future perspective, the implementation of this approach could strengthen the integration of pharmacological review strategies, ensuring a more comprehensive and safer management of medications.
